## 8. Statistical analysis plan

### 8.1. Sample size justification

The sample size was calculated to be able to accept the main hypothesis (H1) with a probability of 5% of committing the type I error and a power of 80%. The calculation was performed with nQuery software (GraphPad Software DBA Statistical Solution, San Diego, CA) and the following parameters were used:

- Significance level  $\alpha = 5\%$
- Allocation ratio  $k = 1$
- Margin of non-inferiority  $\delta = 5^\circ$
- standard deviation  $\sigma = 7^\circ$ 
- Power  $(1 - \beta) = 80\%$

The sample size should be 25 per group, so a total of 50 patients. On the other hand, a loss to follow-up of 15% is anticipated. We will therefore need 29 patients per group for a total of 58 patients.

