## 4. Objective and assumptions

**The general objective** of the project is to validate the new CAD/CAM brace design method integrating the optimization of immediate correction.

**Primary Hypothesis (H1)** : After 1 year and 2 years of use, the out-of-brace correction, as measured by Cobb's angle, from the Test braces will be non-inferior to the Control braces. The non-inferiority margin will be 5 degrees.

**Secondary hypothesis (H2)** : The immediate and medium-term (1 and 2 years) failure rate of treatment will be 10% lower for Test braces compared to Control braces. There are three different types of failures:

1. Mid-term failure (1 and 2 years) – relative progression : A progression of the out-of-brace Cobb angle of 5 degrees or greater than the value measured at visit 1.
2. Intermediate (study duration) failure – absolute progression : A progression of the Cobb angle of the main off-brace curvature to greater than 45 degrees (SRS failure criterion).
3. Medium-term failure (duration of the study) – surgery : Stopping treatment with a brace and a decision to have surgery (AVBGT or fusion).

**Secondary hypothesis (H3)** : The quality of life of patients wearing Test braces in the medium term, as measured with the SRS-22r questionnaire, will be non-inferior to that of patients wearing control braces. The non-inferiority margin will be 10%.

**Secondary hypothesis (H4)** : The immediate in-brace correction of the Cobb angle of the Test brace will be no less than that of the control brace. The non-inferiority margin will be 5 degrees.

The effects measured (dependent variables) are as follows:

| Effects measures                                                         | Descriptions                                                                           |
|--------------------------------------------------------------------------|----------------------------------------------------------------------------------------|
| Major                                                             |                                                                                        |
| Cobb angle off brace (Initial, 6 months, 1 year, 2 years).               | Measure using low-dose EOS radiography to assess the evolution of scoliosis.           |
| Secondary                                                         |                                                                                        |

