## **6. Methodology**

### **6.1. Study design**

A prospective, double-blind, non-inferiority, controlled and randomized clinical trial will be conducted to assess the effectiveness of a new orthopedic brace design platform. Fifty-eight patients will be recruited at the CHU Ste-Justine orthopedic clinic. The study will be divided into two phases. The first phase will use a crossover design to assess the immediate correction of both types of brace. The second phase will use a parallel design with a 1:1 allocation to assess the mid-term correction.

In phase 1, each patient will try on each type of brace with a “control: test” or “test: control” trial sequence. Immediate correction in braces will be assessed. During phase 2 each patient will use one of the two types of braces for a period of two years. There will be a renewal of the brace after 6 or 12 months based on updated spine x-rays and a new trunk geometry. This is in order to consider the growth of the patient and the inherent changes in the patient's body and the scoliotic deformity. Taking into account that all patients do not follow the same growth, renewal of the brace may sometimes be necessary before 12 months (for example after 6 months following a rapid growth spurt). In this case, the brace will be renewed before the end of 12 months to ensure adequate follow-up of the treatment by the patient. If the patient is part of the test group, the optimization of the correction will be redone.

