### 8.3. Analysis of primary hypothesis H1

The analysis of primary hypothesis H1 will have the off-brace Cobb angle as the dependent variable and the type of brace worn as the independent variable. The 95% confidence interval of the difference in correction between the test brace and the control brace will be constructed and compared to the non-inferiority margin.

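### The 25 per group in section 8.1 gives 80% power only for a one-sided 5% test; under the 95% confidence interval of section 8.3, read two-sidedly, power on the same assumptions is about 70%

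*Protocol*

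**What the plan says.** Section 8.1 states that the sample size serves the main hypothesis H1 "with a probability of 5% of committing the type I error and a power of 80" per cent. Its inputs are a significance level of 5%, 1:1 allocation, a margin of 5 degrees and an SD of 7 degrees, the last taken from a previous randomised trial by the same group. It does not say whether the 5% is one-sided or two-sided, and it gives no assumed true difference. The result is: "The sample size should be 25 per group, so a total of 50 patients". Because "a loss to follow-up of 15% is anticipated", the section then concludes: "We will therefore need 29 patients per group for a total of 58 patients".

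Section 4 gives the same margin for H1: "The non-inferiority margin will be 5 degrees". Section 6.1 confirms that the medium-term comparison is between parallel groups: "The second phase will use a parallel design with a 1:1 allocation to assess the mid-term correction".

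Section 8.3 sets the decision rule for H1: "The 95% confidence interval of the difference in correction between the test brace and the control brace will be constructed", and that interval is then compared with the margin. The interval is not called one-sided. The protocol nowhere mentions a 90% interval, a one-sided bound or a one-sided test.

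**The concern.** In a non-inferiority comparison only one limit of the interval matters. A two-sided 95% interval leaves 2.5% beyond that limit, so comparing it with the margin is a one-sided 2.5% test. A one-sided 5% test corresponds to a two-sided 90% interval. If section 8.1 used 5% in one tail while section 8.3 uses a two-sided 95% interval, the quoted power does not belong to the test that will be run.

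Two things are at stake. First, a test brace that is truly equivalent would miss the claim about 3 times in 10, not 2 in 10. Second, some data sets would be a success under the rule implied by 8.1 and a failure under the rule in 8.3. Which rule governs should be settled before anyone sees the results.

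**Working it through.** **Inputs.** From section 8.1: margin 5 degrees, SD 7 degrees, 1:1 allocation, target power 80%, alpha 5% with sidedness unstated, 25 per group before dropout, 15% loss, 29 per group enrolled. From section 8.3: a 95% confidence interval compared with the margin. Assumption: true difference 0. The protocol does not state it, but it is the value that reproduces 25.

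**1. Reproducing the 25.** Normal approximation: n per group = 2 × (z for alpha + z for power)² × SD² / margin².
- One-sided 5%: 2 × (1.645 + 0.842)² × 49 / 25 = 24.2, so 25.
- One-sided 2.5%: 2 × (1.960 + 0.842)² × 49 / 25 = 30.8, so 31.

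The stated 25 matches the first and not the second.

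**2. Exact power (noncentral t).** With n per group, df = 2n − 2 and the noncentrality is 5 / (7 × √(2/n)). At n = 25 the standard error is 7 × √(2/25) = 1.98 degrees and the noncentrality is 5 / 1.98 = 2.53.

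| Evaluable per group | One-sided 5% (90% CI) | One-sided 2.5% (two-sided 95% CI) |
|---|---|---|
| 24 | 78.6% | 67.8% |
| 25 | 80.1% | 69.7% |
| 29 | 85.1% | 76.2% |
| 31 | 87.2% | 79.0% |
| 32 | 88.1% | 80.3% |

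In the one-sided 5% column, 25 is the smallest n that reaches 80%, which identifies the test behind section 8.1. In the other column 25 gives 69.7%, and 32 is the smallest n that reaches 80%.

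**3. Where the two rules part.** With 25 per group and an observed SD of 7, the critical t values on 48 df are 1.677 (one-sided 5%) and 2.011 (one-sided 2.5%). Non-inferiority is shown if the observed shortfall of the test brace is below 5 − 1.677 × 1.98 = 1.68 degrees under the first rule, and below 5 − 2.011 × 1.98 = 1.02 degrees under the second. An observed shortfall between 1.02 and 1.68 degrees passes one rule and fails the other.

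**4. Enrolment implied by 80% power under the two-sided 95% interval.** 32 / 0.85 = 37.6, so 38 per group or 76 in total, against the planned 58.

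**5. Dropout line.** 25 / 0.85 = 29.4, so 30 per group. The stated 29 equals 25 × 1.15 = 28.75 rounded up. It leaves 29 × 0.85 = 24.65 evaluable per group, where power is 69.0% instead of 69.7% (two-sided 95% interval) or 79.6% instead of 80.1% (one-sided 5%).

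**6. Sensitivity at 25 per group, two-sided 95% interval.** SD 6 gives 82.3% and SD 8 gives 58.1%. A true advantage of 1 degree for the test brace gives 84.4%; a true disadvantage of 1 degree gives 50.8%.

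**The case against.** The strongest reply is that sidedness is unstated, not contradicted. If section 8.3 means a one-sided 95% interval, the two sections agree, 25 per group is correct, and the only defect is a missing word. This is arithmetically right. But an unqualified 95% confidence interval is conventionally two-sided, and nothing in the protocol points to the other reading. Even on that reading, the sidedness would have to be written down.

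A second reply is that 70% depends on assumptions. It does: step 6 shows how far power moves with the SD and the true difference, and section 8.2 places all randomised patients in the intention-to-treat analysis, so more than 25 per group might contribute. That argues for attaching the conditions to the figure. It does not rescue the stated 80%, because on section 8.1's own SD, with a zero difference, even 29 evaluable per group reach only 76.2%.

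A third reply is that adjusting for the baseline angle would recover the power. It could, if the residual SD fell to about 6.2 degrees. Read as a baseline-to-outcome correlation, this is √(1 − (6.18/7)²) = 0.47. A reader might infer that no change in enrolment is therefore needed. The protocol does not support that. It gives no correlation. The conversion holds only if the 7 degrees is the SD of the follow-up angle, and it may be the SD of change, since section 8.3 speaks of a difference in correction. Section 8.3 also names brace type as the only independent variable.

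Finally, the two-sided 95% interval is the stricter rule, so there is no excess risk of a false non-inferiority claim. That stands.

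**Conclusion.** The sizing and the success rule for H1 do not match as written. With SD 7 degrees, margin 5 degrees, a true difference of 0 and an unadjusted comparison, 25 evaluable per group give 80.1% power for a one-sided 5% test but 69.7% for a two-sided 95% interval. The conclusion rests on reading that interval in the usual two-sided way.

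Three stronger readings should be resisted:
- That the power of the trial is 70% without qualification. The figure belongs to the assumptions just listed.
- That the type I error is inflated. Under the two-sided 95% interval it is 2.5% in the relevant tail, below the stated 5%.
- That the dropout slip matters in its own right. It is a gap of 25 − 24.65 = 0.35 patient per group and moves power by less than one percentage point.

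**What to change.** Make sections 8.1 and 8.3 agree, in one of two ways, before the outcome data are examined:

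- Keep the two-sided 95% interval in 8.3, say that it is two-sided, and restate the power in 8.1 as about 70% with 25 evaluable per group, assuming SD 7 degrees and a true difference of 0.
- Or state a one-sided alpha of 5% in 8.1 and change 8.3 to a two-sided 90% interval (equivalently a one-sided 95% bound). The 80% then stands, at the price of a less strict success rule.

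Either way, write down the assumed true difference. If the sponsor wants to cite baseline adjustment as restoring 80% under the 95% interval, the text should call this conditional on a residual SD of about 6.2 degrees and give evidence for it. If 80% is wanted under the unadjusted two-sided 95% interval, 32 evaluable per group are needed, about 76 enrolled in total at 15% loss.

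Correct the dropout line as a minor edit: 25 evaluable at 15% loss requires 30 per group; alternatively, keep 29 and state that it tolerates a loss of 4/29 = 13.8%.

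Either of the two main options costs only wording. The first makes the stated power less favourable; the second makes the test less strict.

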### 8.2. Types of analyzes

There will be two types of data analysis: an intention-to-treat (ITT) analysis and a per-protocol (PP) analysis. Data analysis by ITT will include all patients who have been randomized. A study on patient compliance shows that, on average, patients wear the night brace 90.7% of the prescribed time (generally 8 hours). For this reason there will also be an analysis of the results by PP which will only include patients who have worn the brace on average for more than 7.2 hours per day. This method of analysis will make it possible to evaluate the correction of the brace if it is worn with good compliance.

### 8.3. Analysis of primary hypothesis H1

The analysis of primary hypothesis H1 will have the off-brace Cobb angle as the dependent variable and the type of brace worn as the independent variable. The 95% confidence interval of the difference in correction between the test brace and the control brace will be constructed and compared to the non-inferiority margin.

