## **7. Randomization**

Patients who meet all the inclusion criteria and no exclusion criteria will be randomized twice independently.

Randomization #1 will be to determine the trial sequence of brace types at Visit #2. Randomization #1 allocation will have a 1:1 ratio for the “test:control” sequence and the “control” sequence. : test ”.

Randomization #2 will be to determine the brace type the patient will use for a period of two years after the visit. The allocation will have a ratio of 1:1 for test and control brace type respectively.

The randomization will be done by the URCO nurse coordinator according to a block allocation of 2, 4 or 6. Neither the engineers nor the orthopedist nor the orthotist will know the brace assigned for phase #2 until these are designed, manufactured and adjusted.

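### Section 8.3 names two different outcomes for H1 and no baseline term, and Section 8.1 does not say which outcome its 7-degree SD describes

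*Protocol*

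**What the plan says.** Section 8.3 has two sentences. The first says the H1 analysis "will have the off-brace Cobb angle as the dependent variable and the type of brace worn as the independent variable". The second says "The 95% confidence interval of the difference in correction between the test brace and the control brace will be constructed" and compared with the margin. H1 itself, in Section 4, is worded in terms of out-of-brace correction at 1 and 2 years, and "The non-inferiority margin will be 5 degrees". Correction is not defined for H1.

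The baseline value is available: the table of measured effects in Section 4 lists "Cobb angle off brace (Initial, 6 months, 1 year, 2 years"), and Section 6.4 schedules the standing EOS radiograph at Visit 1. Section 6.3 admits curves from 20 to 40 degrees. Section 7 gives blocks of 2, 4 or 6 and 1:1 allocation, and mentions no stratification on curve size.

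Section 8.1 sizes the trial for H1 "with a probability of 5% of committing the type I error and a power of 80" per cent, with a 5-degree margin and a single SD of 7 degrees taken from a cited earlier trial. It does not say whether that is the SD of the follow-up angle or of the change.

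**The concern.** The follow-up angle and the change from Visit 1 are not interchangeable as outcomes. Their SDs differ, so the sample size may fit one and not the other, and in a realised trial they can give different point estimates. The two sentences of Section 8.3 leave both open for the primary hypothesis.

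The only explanatory variable named is brace type. Curve size at entry can be expected to predict curve size later, and neither the allocation nor the stated model uses it. With about 25 patients per arm, the baseline spread stays in the error term if the raw angle is analysed, and a chance baseline difference of 2 or 3 degrees carries into a comparison judged against 5 degrees. At stake is the precision of the primary non-inferiority comparison, together with a choice of outcome that could be made after the data are seen.

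**Working it through.** **Inputs from the protocol.** Margin 5 degrees, SD 7 degrees, power 80%, alpha 5% with sidedness not stated, 1:1 allocation, 25 evaluable per group (Section 8.1); 95% CI (Section 8.3); entry range 20 to 40 degrees (Section 6.3).

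**Assumptions, because the documents give no figure.** Baseline SD 4 to 5.8 degrees, where 5.8 is an even spread over the entry range: 20/√12 = 5.77. Correlation ρ between Visit 1 and follow-up angle, 0.5 to 0.7. True difference zero.

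**Reproducing the plan's figure.** n per group = 2 × 7² × (z₁₋α + z₀.₈)² / 5².
- One-sided 5%: 98 × (1.645 + 0.842)² / 25 = 24.2, so 25. This is the stated figure.
- One-sided 2.5%, the level of a two-sided 95% CI: 98 × (1.960 + 0.842)² / 25 = 30.8, so 31 (32 with the t distribution).

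The stated size therefore assumes one-sided 5% and no baseline adjustment. Both levels are shown below so that the effect of baseline is not confused with the difference in alpha. Power comes from the noncentral t distribution with n = 25 per arm and noncentrality 5 / (SD × √(2/25)).

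**Case A: 7 degrees is the SD of the angle, equal at baseline and follow-up.**
Change-score SD = 7√(2(1−ρ)). ANCOVA residual SD = 7√(1−ρ²).

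| Analysis | SD | Power, 95% CI | Power, one-sided 5% |
|---|---|---|---|
| Raw angle | 7.0 | 70% | 80% |
| Change, ρ = 0.5 | 7.0 | 70% | 80% |
| Change, ρ = 0.7 | 5.4 | 89% | 94% |
| ANCOVA, ρ = 0.5 | 6.1 | 82% | 89% |
| ANCOVA, ρ = 0.7 | 5.0 | 93% | 97% |

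**Case B: 7 degrees is the SD of change, and change is independent of baseline.**
Raw-angle SD = √(7² + baseline SD²), which is 8.1 for a baseline SD of 4 and 9.1 for 5.8. The ANCOVA residual SD is 7.0, the same as for change.

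| Analysis | SD | Power, 95% CI | Power, one-sided 5% |
|---|---|---|---|
| Raw angle, baseline SD 4 | 8.1 | 57% | 70% |
| Raw angle, baseline SD 5.8 | 9.1 | 48% | 61% |
| Change or ANCOVA | 7.0 | 70% | 80% |

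**Chance imbalance.** The SE of the baseline difference is SD × √(2/25): 1.1 degrees for SD 4 and 1.6 for SD 5.8. The 95% ranges are about ±2.2 and ±3.2 degrees, roughly half the margin.

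**Why ANCOVA settles the conflict of outcomes.** Write the follow-up angle as Y = a + bX + τZ + error, with X the Visit 1 angle and Z the brace. Correction is X − Y = −a + (1−b)X − τZ − error. With X in the model, the brace effect and its SE are the same for both outcomes, apart from sign.

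**The case against.** A reader might infer that H1 will simply be analysed as the raw follow-up angle and that power is therefore 48%. The protocol does not support that. The second sentence of Section 8.3 and H1 in Section 4 both speak of correction, which most naturally means change from the Visit 1 angle; on that reading the first sentence may only name the measurement. In Case B a change score already does as well as ANCOVA, and the 48% appears only if the second sentence is set aside. That figure also includes the loss from pairing a one-sided 5% sample size with a 95% CI, which has nothing to do with baseline. At the alpha that reproduces the stated 25, the same extreme case gives 61% against 80%.

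It can also be said that omitting a covariate is no error: the unadjusted randomised comparison is unbiased on average, its CI already allows for baseline variation, and covariates are often left to a statistical analysis plan. This stands as far as validity goes, and the absence of a covariate would not be a finding by itself. What it does not answer is that Section 8.3 states two outcomes for the primary hypothesis and Section 8.1 attaches one SD to neither. Nor does reading correction as an unadjusted change score recover all the precision: in Case A at ρ = 0.5 it gains nothing over the raw angle (70% against 82% for ANCOVA). At ρ = 0.7 the gap is small (89% against 93%).

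**Conclusion.** The point holds as an inconsistency in the definition of the H1 outcome, with an avoidable loss of precision; it is not a source of bias. The inconsistency is in the text and needs no assumption.

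The size of the loss does depend on assumptions. With the planned 95% CI, ANCOVA gains 12 to 23 percentage points over the raw angle in Case A (70% to 82 or 93%) and 13 to 22 in Case B (57 or 48% to 70%). Over an unadjusted change score it gains 12 to 4 points in Case A and nothing in Case B. Which case applies cannot be decided from the protocol, because the meaning of the 7 degrees rests on a cited trial that is not at hand. The change should be made, but the trial's validity does not depend on it.

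**What to change.** In Section 8.3, define correction as the Visit 1 off-brace Cobb angle minus the off-brace Cobb angle at the time point. Estimate the brace difference in off-brace Cobb angle at each H1 time point, 1 and 2 years, by ANCOVA with the Visit 1 off-brace Cobb angle as covariate, and compare the adjusted difference and its CI with the 5-degree margin. In Section 8.1, state which quantity the 7-degree SD describes.

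The cost is a few sentences and one degree of freedom; no extra data, visits or patients are needed. The adjustment does not require dropping the 1-year time point. Two neighbouring matters are separate points and should be decided on their own: whether brace type means the brace worn or the brace randomised, and the mismatch between the one-sided 5% sample size and the 95% CI.

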#### 8.4. Analysis of secondary hypothesis H2

The analysis of secondary hypothesis H2 will have the treatment failure rate as the dependent variable and the type of brace worn as the independent variable. The incidence of failures will be presented with a Kaplan-Meier curve, the statistical analysis will be done with a log-rank test.

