#### Does the brace work?

The Scoliosis Research Society recommends wearing the TLSO 20-23 hrs/day until maturity in young people (Risser index 0 to 2), with a moderate curve (25-40°). Although used for >60 years, the effectiveness of the brace has been repeatedly questioned by the Canadian Task Force on Preventive Health Care due to lack of evidence, leading to the withdrawal of school screening for AIS in Canada. We demonstrated that this decision was harmful, causing a significant increase in patients referred too late to benefit from the brace (current 19% vs 1% at screening) with surgery as the only option, without changing useless referrals (39% vs. 37%).

In 2013, the BrAIST study, a multi-center randomized controlled trial (RCT) confirmed the effectiveness of TLSOs: 28% of treated subjects progressed beyond 50° vs 52% of untreated (OR= 1.93 [1.08-3.46] in favor of the brace). The study, which became “Gold Standard”, was interrupted by the NIH given the demonstrated superiority of the brace. A meta-analysis in 2019 reconfirmed the efficacy and safety of the treatment of idiopathic scoliosis by bracing.

For night braces, such as the Providence brace, a randomized study in 2014 demonstrated that these braces could reduce the progression of scoliosis in patients with curves below 25 degrees. More recently, a literature review and meta-analysis showed that night braces had a success rate of 78.7% versus 73.2% for full-time braces such as TLSO braces. The latest data in the literature therefore show that there is a clinical equivalence in the treatment with a TLSO brace and the night brace.

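### H2 claims a failure rate 10% lower without saying on which scale, and section 8.4 plans only a log-rank test of equal curves, which does not estimate the reduction

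*Protocol*

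**What the plan says.** Protocol section 4 puts a number on H2: "failure rate of treatment will be 10% lower for Test braces compared to Control braces". It refers to immediate failure and to failure at 1 and 2 years, and lists three types of failure: relative progression, absolute progression and surgery. It does not say whether the 10% is absolute or relative.

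Section 8.4 presents the incidence of failure as a Kaplan-Meier curve and adds that "the statistical analysis will be done with a log-rank test". It names no effect estimate, interval or decision rule. Sections 8.3, 8.5 and 8.6 (H1, H3 and H4) each plan a 95% confidence interval to be compared with a margin.

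Section 8.1 sizes the trial for the primary hypothesis only, at 80% power and a 5% significance level. Its result reads: "The sample size should be 25 per group, so a total of 50 patients". Loss to follow-up raises this to 29 per group (58 in total). No failure rate, event count or power is given for H2.

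The only failure figures are in the background (section 2, on whether bracing works). One is a meta-analysis in which "night braces had a success rate of 78.7" per cent. The other is a randomized trial of full-time bracing in which 28% of treated subjects progressed beyond 50°.

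**The concern.** H2 is a statement about size, and the planned test is not. The null hypothesis of a log-rank test is that the two failure curves coincide over the whole follow-up. Rejecting it shows that they differ, not that the reduction is 10%. Failing to reject it does not count against a 10% reduction. The test also gives no result specific to 1 year or 2 years, the times that H2 names.

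The unstated scale adds to this. Two readers could take the same result and disagree on whether H2 was met, because the target differs almost fivefold between the two readings.

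Failure covers progression and surgery, so it matters to patients and clinicians. With few events expected, the likely output of section 8.4 is a non-significant p-value with no statement of how large a difference, in either direction, remains compatible with the data.

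**Working it through.** **1. The plan's own figure.** Section 8.1 gives σ = 7°, δ = 5°, α = 5% and 80% power. The normal formula n = 2σ²(z₁₋α + z₀.₈₀)²/δ² at one-sided 5% gives 2 × 49 × (1.645 + 0.842)²/25 = 24.2, so 25 per group, as stated. At one-sided 2.5% it gives 30.8, so 31. The 29 per group follows from 25 × 1.15 = 28.75. All of this concerns H1; there is no H2 figure to reproduce.

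**2. Inputs for H2.**
- Patients per group: 25 evaluable and 29 randomized (section 8.1), with 1:1 allocation (section 7).
- Control failure: not given. Two values are assumed from section 2: 100 − 78.7 = 21.3%, and 28%. Neither source is shown to use the failure criteria of H2.
- Sidedness: not given. Two-sided 5% matches the 95% intervals of sections 8.3, 8.5 and 8.6; one-sided 5% is what reproduces the 25 per group. Both are shown.

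**3. The two readings of 10%.** At 21.3% control failure, 10 points gives 11.3% with Test braces. A 10% relative reduction gives 21.3 × 0.9 = 19.2%, a difference of about 2.1 points.

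**4. Log-rank power for a true 10-point reduction.** Expected events d = n(p₁ + p₂); HR = ln(1 − p₂)/ln(1 − p₁); power = Φ(√d × |ln HR|/2 − z).

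Example with p₁ = 0.213, p₂ = 0.113, n = 25: d = 8.15; HR = 0.120/0.240 = 0.50; √8.15 × 0.692/2 = 0.988; Φ(0.988 − 1.960) = 16.5%.

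| Control vs Test | n per group | Events | HR | Two-sided 5% | One-sided 5% |
|---|---|---|---|---|---|
| 21.3% vs 11.3% | 25 | 8.1 | 0.50 | 16.5% | 25.6% |
| 21.3% vs 11.3% | 29 | 9.5 | 0.50 | 18.5% | 28.1% |
| 28% vs 18% | 25 | 11.5 | 0.60 | 13.4% | 21.5% |
| 28% vs 18% | 29 | 13.3 | 0.60 | 14.9% | 23.4% |

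A simulated log-rank test (20,000 runs, exponential failure times, six-monthly detection, two years) agrees: about 16% and 18% in the first two rows and 13% and 14% in the last two, at two-sided 5%. For 80% power, 4(1.960 + 0.842)²/(ln HR)² gives 66 events at HR 0.50 and 124 at HR 0.60, against 8 to 13 expected.

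**5. Sensitivity.** If 10% is relative, power is about 4 to 6% at the same two control rates (two-sided). For an absolute reduction at two-sided 5%, power is 11 to 13% at 40% control failure and 21 to 28% at 15%. None of these figures allows for the brace switching that section 6.5 permits, which would dilute an intention-to-treat contrast.

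**6. What an interval would show.** Half-width = 1.96 × √[p₁(1 − p₁)/n + p₂(1 − p₂)/n].
- 21.3% vs 11.3%: 20.3 points (n = 25), 18.8 (n = 29).
- 28% vs 18%: 23.2 points (n = 25), 21.5 (n = 29).

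This is about twice the claimed effect.

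**7. Could the interval confirm a 10-point reduction?** Take observed control failure of 21.3% and no Test failures at all. With n = 25 the half-width is 1.96 × √(0.213 × 0.787/25) = 16.0 points, a lower limit of 5.3. With n = 29 it is 14.9 points, a lower limit of 6.4. Both are below 10. At 28% the same extreme result gives 28 − 17.6 = 10.4 (n = 25), barely above 10, from a formula that counts no variance in the Test arm. In practice, no.

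**The case against.** The strongest reply is that H1, H3 and H4 are non-inferiority hypotheses, which need an interval against a margin, whereas H2 is directional and has no margin. If 10% is simply the effect expected, testing for any difference with a log-rank test is conventional, and the change of method is not an inconsistency. This stands in part: section 4 does not say that 10% is a threshold to be proven. But the hypothesis still carries a number on an undefined scale, and the planned inference does not speak to that number under either reading.

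Low power for a secondary hypothesis is not an error either. Section 8.1 claims power for H1 only. This stands in full: the power figures show what a null result would be worth and do not mean that the sample size is wrong.

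A statistical analysis plan could also add an interval, and the Kaplan-Meier curve already displays cumulative failure by group. Detail left to that plan is not the complaint. The protocol itself states the hypothesis and names the test, and the two do not match.

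Finally, an interval will not confirm a 10-point reduction at this size, as step 7 shows. That is correct. The gain is an estimate with its imprecision visible, not a confirmatory answer.

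**Conclusion.** The point holds in two parts that need no assumed rate: the 10% in H2 has no stated scale, and the only inference planned in section 8.4 neither estimates the reduction nor shows whether it reaches 10%.

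The size rests on assumptions. With control failure of 21 to 28%, a true 10-point reduction and 25 to 29 per group, power is about 13 to 18.5% at two-sided 5% and 21 to 28% at one-sided 5%, with an interval of about ±19 to 23 points. A non-significant log-rank result would be uninformative.

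A reader might infer more than the protocol supports, in three ways.
- That the test would miss a true H2 effect more than 80% of the time, as a fact. This needs a two-sided 5% test and, for an absolute reduction, control failure of about 20% or more. The protocol fixes neither. At one-sided 5% the figure is 72 to 79% for the two control rates used here.
- That the trial is wrongly sized. The sample was calculated for H1, and H2 is secondary.
- That a null result would be used to support H1. Nothing says so; section 8.3 decides H1 by its own interval.

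The primary analysis and the sample size are unaffected. The change is still worth making, because it is nearly free and H2 concerns an outcome that readers will look at.

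**What to change.** - **Section 4, H2:** state whether 10% means percentage points or a relative reduction.
- **Section 8.4:** make the H2 result the between-group difference in Kaplan-Meier cumulative failure at 1 year and at 2 years, each with a 95% confidence interval. Keep the log-rank test as supportive.
- **Section 8.4 or 8.1:** label H2 as exploratory because the sample was sized for H1 only, and state that a non-significant result is not evidence of equal failure.

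The cost is a few sentences, with the same data and no extra patients or visits. The downside is that the H2 claim becomes visibly weaker: the interval will be wide and will not be able, in practice, to confirm a 10-point reduction with 25 to 29 patients per group.
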